#### Treatment group

Inmates assigned to the treatment group will participate in the DDMI-IGT continuum. Between four and eight groups of participants will complete the DDMI-IGT treatment during the pilot RCT, depending on how many participants are enrolled in each IGT cycle. No more than 8 inmates will participate in IGT at any given time. In addition to the DDMI-IGT treatment continuum, inmates in the treatment condition also will receive any and all necessary usual care across jail and community settings.

#### Control group

Inmates assigned to the control condition will receive treatment as usual (TAU) and will not be enrolled in the DDMI-IGT treatment continuum. That is, inmates in the control group will continue to receive any and all usual care services across jail and community settings, as do any inmates regardless of participation in this study.

As noted, participants across both conditions will receive any and all clinically indicated usual care services across the jail and community sites. The delivery of those services, including their discontinuation or modification if needed, will be based on the treating clinician’s judgement and appropriate treatment planning within the context of the jail and community-based treatment system supporting the implementation of this project.

### Assessment schedule and measures

#### Open trial

To address Aim 1, we will collect qualitative and quantitative data regarding acceptability of, fidelity to, and feasibility of the treatment from inmates and clinicians during the uncontrolled open trial (see Table 1). *Acceptability* will be evaluated to determine participant and clinician satisfaction with the communication protocols and the DDMI-IGT treatment continuum, using the Client Satisfaction Questionnaire-8 (CSQ-8) [46, 47], Narrative Evaluation of Intervention Interview (NEII) [48], semi-structured interviews, focus groups, and administrative records. *Fidelity* will be examined at the end of the open trial to determine the degree to which clinicians adhered to the adapted treatment programs based on a review of audio recorded treatment sessions and DDMI (Moyers, Martin, Manuel, Miller, Ernst. Revised global scales:motivational interviewing treatment integrity 3.1. 1 (MITI 3.1. 1). Unpublished.) and IGT [28] Adherence Forms. *Feasibility* will be evaluated to determine the success of treatment implementation, enrollment, and coordination, as well as the feasibility of research and communication protocols, using data collected from semi-structured interviews, focus groups, and administrative records.

#### Pilot randomized controlled trial

To address Aim 2, we will collect inmate and community partner outcome data to evaluate treatment effectiveness, feasibility, and acceptability of the pilot RCT (see Table 1). Treatment *effectiveness* will be assessed using three categories of outcome variables: (1) clinical, including inmate substance use, psychiatric symptoms, health status, service use, and quality of life; (2) criminal justice, including contacts and re-arrest, which will serve as the primary outcomes of the pilot RCT; and (3) treatment preferences. These outcomes will be assessed five times, including an in-jail baseline assessment and four additional community-based assessments spanning 1 week to 5 months after jail discharge (see Table 1). In addition to these effectiveness outcomes, we additionally will measure implementation outcomes related to the interventions and protocols. Specifically, *feasibility* and *acceptability* will be assessed using the same measures from the open trial, including inmate exit interviews, community partner focus groups, and administrative record review. The primary explanatory variable will be the experimental condition; that is, whether participants were assigned to either the treatment group (DDMI-IGT + TAU) or the control group (TAU only). Additionally, we will collect sociodemographic data for participants, including diagnosis, race/ethnicity, age, and sex, obtained through clinical and administrative records. Inclusion of these variables will allow examination of potential differences in treatment outcome as a function of each variable while controlling for sociodemographic factors in statistical analyses.

### Analytic plan and statistical methods

#### Aim 1

We will conduct Aim 1 analyses to evaluate qualitative and quantitative data regarding the feasibility of, fidelity to, and acceptability of the DDMI-IGT continuum and protocols. All transcribed qualitative data from interviews and focus groups will be coded according to coding guidelines which will concentrate on deductive themes focusing on the feasibility and acceptability of treatment programs and protocols. A subset of transcripts will be coded independently by two team members in Atlas.ti using iterative content analysis [49]. Discrepancies will be resolved by refining codes and definitions through team discussion, until >90% agreement is reached. After all transcripts are coded, data will be searched and data output analyzed to build an understanding of feasibility and acceptability and possible revisions. For example, potential broad category codes could include “feasibility challenges,” “feasibility facilitators,” and “feasibility recommendations” with lower level codes indicating data collected from providers and participants. Low-level codes will be grouped into broader categories when possible. Additionally, we will calculate and review descriptive statistics of administrative data (e.g., call logs, frequency of inter- and intra- communication, average number of treatment sessions attended) to assess treatment and protocol feasibility. Findings will be used to refine treatment adaptations and protocols as needed prior to conducting the pilot RCT.

#### Aim 2

We will examine baseline clinical, legal, and demographic differences between groups to determine if RCT treatment group randomization was successful [50]. Additionally, we will assess demographic differences between consenters and refusers, reasons for refusal, and retention rates.

To address Aims 2.1 and 2.2 regarding the feasibility and acceptability of and fidelity to the treatment and protocols, we will integrate qualitative and quantitative data by transforming qualitative data (e.g., noting the occurrence of themes in interviews and focus groups) to support or refute quantitative results (i.e., data merging) [51–53]. All qualitative data collected from inmates, clinicians, and jail personnel will be analyzed using the coding approach described above for Aim 1. Feasibility will be evidenced by the acceptable rates of participant exposure (85% complete DDMI; attend >1 IGT session/week) and retention (>75% completion rate) in the treatment continuum [54–56]. Acceptability to clinicians will be evidenced by focus group and interview themes reflecting an overall more positive than negative perception (e.g., endorsement for continuing the program, even if minor inconveniences are noted). Acceptability to inmates will be evidenced by average CSQ-8 item scores >3 [57] and interview themes reflecting more positive than negative perceptions. Fidelity will be evidenced by mean item scores >4 (Moyers, Martin, Manuel, Miller, Ernst. Revised global scales:motivational interviewing treatment integrity 3.1. 1 (MITI 3.1. 1). Unpublished) for the DDMI and >3 [28] for the IGT fidelity ratings.

We will use a generalized linear mixed model (GLMM) to address Aim 2.3 regarding the effectiveness of the DDMI-IGT treatment condition. In addition to inferential tests of significance and associated confidence intervals, effect sizes will be estimated. Our approach will be extended to estimate standardized differences between the means for planned contrasts in the amount of change that has taken place between pairs of times. Effect sizes will be ranked from highest to lowest, tabled, and graphed. Mindful of concerns regarding estimation of effect sizes in pilot studies and the accuracy of estimates of replication, our goal will be to identify a consistent pattern in the results that will help determine the choice of primary outcome measures in future research [58, 59].

Although not a primary aim of this study, an important clinical question is the extent to which the intervention might be differentially effective as a function of inmate characteristics at treatment entry. We believe four factors might moderate intervention effectiveness and thus merit attention in our future research: diagnosis or psychiatric severity [8, 60]; substance use, including differential use of alcohol or drugs [8, 61], psychiatric symptoms [61–63]; and criminal [62, 63] or antisocial history, including disinhibition [64]. Following our GLMM analyses, we will undertake exploratory supplemental analyses by fitting expanded statistical models that include these variables as additional main effects and, more importantly, as interactions with treatment condition, to assess the extent to which each might moderate the treatment condition effect.

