#### Pilot randomized controlled trial

For the pilot RCT, all inmates who consent to participate will be randomly assigned to one of two conditions: the DDMI-IGT treatment group or the control group. After consent, participants will receive their group assignment. All inmates will be given a preassigned study ID, each associated with assignment to either the treatment or control group, as determined by a random number generator. Participants will be informed of their allocation to study condition by the research interviewer. Allocation is not concealed, as participants will be asked to provide feedback on their satisfaction with, and preferences for, treatment (see Table 1).

**Table 1 Tab1:** Uncontrolled open trial and pilot RCT measures and assessment schedule

					Assessment schedule					
Aim	Construct	Measure	Measure characteristics	Informant	OT	RCT				
						T0	T1	T2	T3	T4
1, 2.1, 2.2	Acceptability	Client Satisfaction Questionnaire-8 (CSQ-8) [49, 50]	8-item measure of satisfaction with DDMI-IGT treatment continuum	Inmates	X				X	
1, 2.1, 2.2	Acceptability	Narrative Evaluation of Intervention Interview (NEII) [51]	16-item interview for evaluating interventions	Inmates	X				X	
1, 2.1, 2.2	Acceptability, feasibility	Focus groups	Semi-structured groups about satisfaction with treatment continuum and protocols; implementation barriers, impact on jail and agencies	Community partners	X				X	
1	Fidelity	DDMI Adherence Form [52]	10-item measure of adherence and competence of DDMI sessions	Community partners	X					
1	Fidelity	IGT Adherence Form [28]	15-item measure of adherence and competence of IGT sessions	Community partners	X					
1, 2.1, 2.2	Feasibility	Exit interviews	Semi-structured interview of treatment success, barriers	Inmates	X				X	
1, 2.1, 2.2	Feasibility	Administrative records	Call logs; number of inter- and intra-agency contacts	Community partners	X				X	
1, 2.1, 2.2	Feasibility	Service Tracking Form	Treatment recruitment; sessions attended in jail, session attending in the community; graduation rates	Community partners	X				X	
2.3	Effectiveness: clinical	Addiction Severity Index (ASI) [53]	27-item measure of alcohol and substance use in prior 30 days, or since last assessment	Inmates		X	X	X	X	X
2.3	Effectiveness: clinical	Brief Psychiatric Rating Scale (BPRS) [71]	18-item measure of psychiatric symptom severity	Inmates		X	X	X	X	X

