### Power analyses

The proposed study will have a small, but appropriate [65] sample size of 60. This study is developmental in nature, which informs how we have chosen to address the choice of error rates and power to detect effects in our clinical and public health outcomes. Prior research suggests small to medium substance use and psychiatric symptom effects of DDMI [25, 27] and IGT [28–30]. Therefore, type I error rate α = 0.15 was chosen so as not to limit power to conduct inferential analyses, giving an 80% chance (1 – β = .80) to detect a difference between the treatment conditions that would explain 9% of the total variance [θ^2^ = .09] in an outcome variable if the null hypothesis were false (calculated using G*Power 3.1 [66]). This approach allows for increased opportunity to detect a smaller effect, while running the risk that the effect will not replicate. This course of action is appropriate for a developmental study and is consistent with prior research involving adults with SMI and preliminary-stage multivariable models [61].

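### Baseline differences cannot show that randomisation succeeded, and the main re-arrest/contacts analysis has no stated adjustment for prior criminal history

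*Protocol article*

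**What the plan says.** The Aim 2 paragraph of *Analytic plan and statistical methods* says the arms will be compared on clinical, legal and demographic variables at baseline "to determine if RCT treatment group randomization was successful". It gives no test, no threshold and no consequence. Under *Participant identification and recruitment*, study IDs are preassigned, "each associated with assignment to either the treatment or control group, as determined by a random number generator".

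Adjustment is described in three places:

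- *Assessment schedule and measures, Pilot randomized controlled trial* lists diagnosis, race/ethnicity, age and sex. It says treatment outcome will be examined "while controlling for sociodemographic factors in statistical analyses". The same paragraph makes criminal justice contacts and re-arrest the primary outcomes.
- The Aim 2.3 text names a generalized linear mixed model (GLMM) with contrasts of change from one assessment to another. It lists no baseline covariates.
- The paragraph after that names possible moderators: diagnosis or psychiatric severity, substance use, psychiatric symptoms, and criminal or antisocial history. These enter as main effects and interactions only in exploratory models that follow the GLMM.

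Table 1 schedules most clinical scales from T0 to T4, but criminal justice records at T4 only.

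**The concern.** The quoted sentence gives the baseline comparison a job it cannot do. Success of randomisation is a property of how assignment was generated and carried out. Chance imbalance is compatible with a perfect process, and apparent balance is compatible with a flawed one.

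The practical stake is how chance imbalance in prognostic factors is handled. In a trial of this size it can be large enough to shift the result. The protection is adjustment chosen in advance, not a verdict on the baseline table. On the stated plan, the history most obviously relevant to re-arrest is compared at baseline and then left to exploratory models, so the primary outcomes are the least protected.

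**Working it through.** **Inputs.** N = 60, outcome α = 0.15, power 80% and 9% of variance explained (*Power analyses*). The documents do not give the allocation ratio, the number of baseline variables or any covariate–outcome correlation ρ. I assume 30 per arm and show ranges for the others.

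**The plan's own figure.** Two-sided α = 0.15, noncentral F(1, 58):

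- f² = 0.09, noncentrality 60 × 0.09 = 5.4: power 80.6%, which matches the stated 80%.
- Strict conversion f² = 0.09/0.91 = 0.0989: power 83.5%, with d = 2√0.0989 = 0.629.

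The point does not depend on this figure; d is used below only for scale.

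**False alarms under sound randomisation.** If each of k independent variables were tested at 0.05, P(at least one significant) = 1 − 0.95^k:

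| k | P |
|---|---|
| 5 | 23% |
| 10 | 40% |
| 15 | 54% |

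Positive correlation among the variables would lower these.

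**Imbalances that would pass.** The standard error of a standardised difference is √(2/30) = 0.258.

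- A difference of 0.4 SD gives t = 0.4/0.258 = 1.55 on 58 df, p = 0.127. It passes at 0.05.
- Chance alone gives an absolute difference above 0.4 SD with probability 12% per variable.
- The 0.05 cut-off is 1.96 × 0.258 = 0.506 SD, so 0.5 SD also passes.
- A real 0.5 SD imbalance, for instance from subverted allocation, would reach p < 0.05 only 49% of the time, and one of 0.3 SD only 21%.

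**What an unadjusted imbalance does (continuous outcome).** The expected shift in the treatment difference is ρ × imbalance. With ρ = 0.5 and 0.4 SD it is 0.5 × 0.4 = 0.20 SD, and 0.20/0.629 = 32% of the design effect.

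The conditional type I error of the unadjusted two-sided test at 0.15 (critical value 1.44), given a 0.5 SD imbalance, follows from z_b = 0.5/0.258 = 1.94. The test statistic then has mean ρz_b and SD √(1 − ρ²):

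- ρ = 0.3: 20%
- ρ = 0.5: 30%

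**What adjustment gains (continuous outcome, d = 0.629, α = 0.15).** Residual SD = √(1 − ρ²). Power is 83.5% at ρ = 0, 86.2% at 0.3, 91.1% at 0.5 and 97.4% at 0.7. These values do not carry over directly to a binary or count re-arrest outcome.

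**Change contrast against baseline adjustment, repeated scales.** Relative to a post-baseline variance of 1, with equal variances at both times, a simple change has variance 2(1 − ρ) and a baseline-adjusted comparison has 1 − ρ²:

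| ρ | Change | Adjusted |
|---|---|---|
| 0.3 | 1.40 | 0.91 |
| 0.5 | 1.00 | 0.75 |
| 0.7 | 0.60 | 0.51 |

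Simple change contrasts do use T0, but less efficiently.

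**The case against.** Several counter-arguments are sound and limit the point.

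- **No test is stated.** The article speaks only of examining differences. A reader might apply the trial's α of 0.15 to the baseline table and quote 1 − 0.85^10 = 80% false alarms. The documents do not support that: *Power analyses* sets 0.15 for outcome analyses, and at 0.15 the 0.4 SD imbalance (p = 0.127) would be flagged rather than missed. The 40% is an illustration only.
- **No consequence is attached.** A reader might infer that covariates will be chosen after seeing the imbalance, or that a sound trial could be declared failed. Nothing in the text says so, and the sociodemographic control is not made conditional on balance.
- **Imbalance is not always chance.** The article says allocation is not concealed, and its objectives include developing ways to randomise in a jail. A gross imbalance is a legitimate, if weak, reason to audit assignment. It still cannot establish success.
- **Adjustment is not absent.** T0 enters through the change contrasts, and severity, substance use and criminal history appear as main effects in the exploratory models. A reader might say the plan ignores baseline clinical values; it does not.
- **A full covariate list may sit in an unseen analysis plan.** Its absence is no fault. What stands is what the article itself fixes: the inference about success, and the placing of criminal history in exploratory models after the main GLMM.

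**Conclusion.** The point holds in two limited parts. First, the stated inference is wrong whether differences are tested or only inspected, and no later document would make that sentence right. Second, as written, the primary re-arrest and contacts outcomes have no stated adjustment for prior criminal history in the main model, although the authors plan both to compare baseline legal variables and to model criminal history later.

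The size is illustrative. Under sound randomisation there is about a 40% chance of at least one p < 0.05 among 10 independent variables, and a 0.4 SD imbalance passes unnoticed. Both figures assume 30 per arm and testing at 0.05. The 20–30% conditional error rates also assume a continuous outcome, a 0.5 SD imbalance and ρ of 0.3 to 0.5. A reader might infer that adjustment removes all chance bias; it deals only with the covariates included. The trial's validity is not in doubt on this ground. It is a worthwhile correction to analysis wording and to the main model.

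**What to change.** 1. In the Aim 2 paragraph, present baseline characteristics by arm descriptively and delete the inference about success. If wanted, say that a gross imbalance will prompt a check of the assignment records.
2. State that the main re-arrest/contacts model includes baseline criminal history whatever the observed balance. Define the measure and its look-back period, which the article does not give. Table 1 lists criminal justice records at T4 only, while the text says outcomes are assessed five times including baseline; reconcile these when defining it.
3. For the repeated clinical scales, state either that T0 is a covariate for the post-baseline responses (and not also a response), or that T0 stays in the response with arm means constrained equal. Either replaces simple change contrasts. Both require T0 to be taken before participants learn their assignment, so confirm that order.
4. Keep the moderator models exploratory.

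**Cost.** Slightly more analysis work and a defined extraction of prior arrests. If events are sparse, the primary model can carry only a few covariates. The precision gain depends on a correlation the documents do not give. No change in sample size or design is needed. The article reports RCT recruitment as ongoing, so on that status the change can be made before outcomes are analysed.

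### Aim 2.3 clinical effect sizes are arm differences in change with no stated adjustment for the T0 score; adjusting T0-to-follow-up contrasts for T0 would gain precision at almost no cost

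*Protocol article*

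**What the plan says.** In the protocol article, *Analytic plan and statistical methods*, Aim 2, a generalized linear mixed model (GLMM) addresses Aim 2.3. The approach is then extended to "estimate standardized differences between the means for planned contrasts in the amount of change that has taken place between pairs of times". The resulting effect sizes are ranked, tabled and graphed, to help choose primary outcomes for later research.

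Three other places bear on how baseline is used:

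- *Assessment schedule and measures*, pilot RCT: diagnosis, race/ethnicity, age and sex are collected so that outcomes can be examined "while controlling for sociodemographic factors in statistical analyses". The outcomes' own T0 scores are not mentioned there.
- *Analytic plan*, moderator paragraph: psychiatric severity, symptoms, substance use and criminal or antisocial history enter after the GLMM analyses, by "fitting expanded statistical models that include these variables as additional main effects" and as interactions with condition. These models are exploratory.
- *Power analyses*: with 60 participants and alpha 0.15, the study has 80% power for "a difference between the treatment conditions that would explain 9% of the total variance" in an outcome variable. The article does not say whether that variable is a follow-up score or a change score.

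Table 1 schedules the ASI, BPRS, SF-12 and quality-of-life scale at T0 and at T1 to T4. T0 is taken in jail and the follow-ups in the community.

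**The concern.** A contrast in change subtracts the whole T0 score. Adjustment subtracts only the part that predicts follow-up. When the correlation between T0 and follow-up is modest, subtraction adds noise, and below 0.5 the change score is noisier than the follow-up score alone. The move from jail to community makes a modest correlation plausible, though the article gives no value.

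The ranked effect sizes are the main product of Aim 2.3. Without adjustment, their intervals are wider than they need be. A chance T0 imbalance between two arms of about 30 is also over-corrected, so regression to the mean enters the estimates. The standardiser is not stated either. If it were the SD of change, the ranking would partly reflect each scale's correlation with baseline rather than the size of the effect.

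**Working it through.** **Inputs from *Power analyses*.** N = 60: "The proposed study will have a small, but appropriate [65] sample size of 60". Alpha: "type I error rate α = 0.15 was chosen so as not to limit power to conduct inferential analyses". Power: "giving an 80% chance (1 – β = .80) to detect a difference between the treatment conditions". Effect: a difference "that would explain 9% of the total variance".

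**Assumptions.** 30 per arm (no allocation ratio is given), a two-sided test, complete data, equal variances at T0 and follow-up, and one pair of times. The correlation rho between T0 and follow-up is not in the article, so a range is shown.

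**Step 1: reproduce the 80%.** Noncentral F with 1 and 58 df and noncentrality N × f².

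- Taking 9% as f² = 0.09 (d = 2 × √0.09 = 0.60): power 80.6%.
- Taking 9% as a share of total variance, f² = 0.09/0.91 = 0.0989 and d = 2 × √0.0989 = 0.629: power 83.5%.
- One-sided on the second reading: 91.9%, which does not match.

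The stated figure is reproduced with a two-sided test and is slightly conservative on the second reading.

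**Step 2: variances.** With follow-up variance set to 1:

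- unadjusted change: 2(1 − rho)
- T0-adjusted: 1 − rho²
- ratio: 2(1 − rho)/(1 − rho²) = 2/(1 + rho)

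At rho 0.3 this is 1.40/0.91 = 1.54; at 0.5, 1.00/0.75 = 1.33; at 0.7, 0.60/0.51 = 1.18.

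**Step 3: power at N = 60, with d = 0.629 on the follow-up score.** The change contrast uses d/√(2(1 − rho)). The adjusted contrast uses d/√(1 − rho²) with 57 df.

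| rho | Change | Follow-up alone | T0-adjusted |
|---|---|---|---|
| 0.3 | 72.6% | 83.5% | 86.2% |
| 0.4 | 77.8% | 83.5% | 88.4% |
| 0.5 | 83.5% | 83.5% | 91.1% |
| 0.6 | 89.6% | 83.5% | 94.3% |
| 0.7 | 95.3% | 83.5% | 97.4% |

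**Step 4: where the change contrast crosses 80%.** With 60 participants, 80% power needs a standardised difference of 0.594. Setting 0.629/√(2(1 − rho)) = 0.594 gives rho of about 0.44. Starting from d = 0.60 gives about 0.49. Starting from an effect with exactly 80% power gives 0.50.

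**Step 5: total N for 80% power (normal approximation), change against adjusted.** 74 against 48 at rho 0.3; 54 against 40 at 0.5; 32 against 28 at 0.7.

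**Step 6: standardiser.** If the SD of change were used, the same true effect of 0.629 would appear as 0.629/√1.4 = 0.53 at rho 0.3 and as 0.629/√0.6 = 0.81 at rho 0.7.

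**The case against.** The strongest reply is that the article does not fix how the GLMM handles T0. T0 is one of five assessments and may enter as a repeated response. If the T0 means are constrained equal across arms, the arm difference in change from T0 to a later time is the arm difference at that time, so the planned contrast and the efficient one coincide. That detail could sit in an analysis plan that is not shown. This stands, and it is why the point is conditional. Having T0 as a response is not enough in itself, however: with free arm-by-time means the contrast is still a change-score comparison, and no constraint is stated.

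A reader might infer that the main model leaves T0 out, or that the trial falls short of its 80% power. The documents support neither. The moderator paragraph concerns severity as an added covariate and does not bar the T0 score from the main model. The shortfall needs both a low rho, which the article does not give, and the 9% read on the follow-up score. If the 9% refers to change, the 80% stands.

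Three further limits also stand:

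- Under randomization, with T0 completed before allocation is disclosed, the change contrast is unbiased over repeated trials. The loss is one of precision.
- Pairs of times without T0 fall outside the argument.
- The primary re-arrest and criminal justice outcomes come from records at T4 in Table 1 and are not affected.

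**Conclusion.** The point holds as an efficiency improvement for the clinical scales, on contrasts that include T0. The article states a change-based estimator and names no T0 adjustment. Without adjustment or a baseline constraint, the variance is higher by 2/(1+rho) for any rho below 1. On the assumptions above, adjustment adds about 14 percentage points of power at rho 0.3, 8 at 0.5 and 2 at 0.7. Adjusted power stays at or above 83.5% at every rho examined.

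It is not a demonstrated error in the power statement, which is reproduced. The change contrast falls below 80% only for rho under about 0.44 to 0.50, and only if the 9% is of follow-up-score variance. The gain is still worth taking in a pilot that set alpha at 0.15 to protect power and that will rank these effect sizes.

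**What to change.** - For the ASI, BPRS, SF-12 and quality-of-life scale, report the arm difference at each of T1 to T4 from the GLMM with the outcome's T0 score as a covariate. A common T0 mean across arms is an alternative if T0 is completed before allocation is disclosed.
- State the order of T0 and disclosure. The article says participants learn their assignment after consent and places T0 at program enrollment, but does not say which comes first.
- Name one standardiser for all ranked effect sizes, for example the pooled T0 SD.
- Say in *Power analyses* whether the 9% refers to a follow-up score or a change score.
- Keep change contrasts, including pairs without T0, as secondary or descriptive.

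The cost is wording, a few lines of model code and one more parameter per outcome. No new data, visits or participants are needed.
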